### I. Research Overview / Background / Rationale

Insomnia is the most common sleep problem, affecting approximately 20-40% of adults worldwide, of which 9-15% meet the diagnostic criteria for insomnia disorderi. 45.4% of respondents in China have experienced varying degrees of insomnia in the past 1 monthii. About 74% of insomniacs report insomnia lasting more than 1 yeariii. Insomnia can be divided into short-term insomnia and chronic insomnia. Short-term insomnia disorders are mostly associated with significant stressors and can mostly resolve on their own with the removal of the stressor or appropriate coping patterns, while some patients can progress to chronicity due to poor coping patterns. The diagnostic criteria for chronic insomnia disorder are: problems falling asleep or maintaining sleep for  $\geq 3$  months ( $\geq 3$  times per week) with impaired daytime functioning, despite the opportunity to sleepiv. Chronic insomnia disorder is difficult to treat and has far-reaching effects.

Insomnia can affect the quality of life, work efficiency and production safety, but also cause a huge social burden, research shows that the health and economic burden of patients with insomnia disorder is 11 times more than those who sleep wellvi. Chronic insomnia disorder (chronic insomnia disorder) is associated with other chronic diseases such as obesity, diabetes, hypertension, cardiovascular disease, sleep apnea, anxiety, depression, etci, vii, viii, Increase the burden on society by causing indirect losses.

Currently, insomnia is treated with medication, cognitive-behavioral therapy, and a combination of the two. Although medication is fast-acting and can improve sleep in the short term, there is no long-term evidence of effectivenessix, Long-term use can result in a variety of adverse effects such as increased drug tolerance and dependence, withdrawal rebound, daytime functional impairment, motor incoordination, and increased risk of falls in hospitalized elderlyx. Multiple moderate and high-quality randomized controlled studies, systematic reviews, etc.xi, xii Cognitive behavioral therapy for insomnia (CBT-I) has been shown to be an effective treatment for insomnia without the adverse effects similar to those of drugs. Moreover, the duration of efficacy of CBT-I is longer than that of drugs, and the positive effects of treatment can last up to 1 year and still have significant clinical significancexiii. Therefore, CBT-I is currently recommended as the first-line treatment for chronic insomnia in adults in both Chinese and foreign authoritative guidelinesii, xiv, xv, or in combination with drug therapy if necessary.

CBT-I is a multimodal cognitive-behavioral therapy that focuses on insomnia and includes sleep hygiene education, stimulus control, relaxation therapy, sleep restriction therapy and cognitive therapy, and typically requires 6-8 weeks of treatment. CBT-I is a therapy with an educational nature and has the advantage of providing patients with tools that can be applied in the future. However, the traditional CBT-I treatment process is complex, financially costly, and requires an experienced and well-trained therapist or physician to have sufficient benefit. While the main treatment sites for insomnia are in primary care, psychiatric-psychological clinics, and sleep clinics, the lack of qualified therapists or clinicians skilled in all treatment components makes CBT-I difficult to obtain. There are operational differences and even irregularities between practitioners that can affect the efficacyxvi. This situation is accentuated by the large population base in China, the large number of insomnia patients, the shortage of medical personnel, and the uneven distribution of medical resources. Therefore, there is an urgent need for new high quality and affordable CBT-I implementation methods with wide coverage.

In recent years, with the popularization of information technology, Internet-based CBT-I has been established and developed to provide convenient, standardized and homogeneous treatment services for insomnia patients, breaking through the limitations of time and space. Networked CBT-I is mainly

divided into two forms: full/partial participation of therapists and full self-help without therapist participation. Full self-help is the most economical way, but it requires high technical requirements and poor compliance. Several RCT studies and meta-analyses have been conducted abroadxvii, xviii show , internet CBT-I can significantly reduce the severity of insomnia, improve sleep efficiency and total sleep time, enhance sleep confidence, and reduce the occurrence of depression compared with the waiting treatment group or the general sleep education group. internet CBT-I has shown its unique advantages and attracted high attention since the global novel coronavirus outbreak in the first half of 2020. Internet CBT-I in China is still in its infancy, and existing ongoing registration studies use a networked CBT-I system with psychoeducation and homework as the main interventions, with the goal of reducing the occurrence of depression and reducing the formation of related suicidal ideation in insomniacs.

The main problems with current networked CBT-I are: 1. Internet-based CBT-I in most clinical studies is implemented through a web-based platform, and there are relatively few digital CBT-I (dCBT-I) implemented using mobile device applications, which are simpler to implement, more flexible, and have a wider audience, and may be more suitable for the reality of our country where economic and cultural development is uneven but smartphones are very popular. 2. poor adherence to fully self-help CBT-I treatment in clinical studies, with a shedding rate of about 20%-45%, may be related to the fact that the software implements education through reading or video but has insufficient interactive features. 3. most web-based CBT-I implementations follow a set sequence of modules one by one, with insufficient individualization of patient response to treatment, which affects efficacy and time to achieve efficacy.

Therefore, digital CBT-I (dCBT-I) treatment based on smartphone application, using intelligent algorithms to increase interactive functions and improve educational experience, may be beneficial to solve the above web-based CBT-I bottlenecks and further accelerate symptom improvement, improve efficacy and treatment adherence. The implementation of dCBT-I through cell phone application is very suitable for China's vast geographical area, the serious imbalance of medical resources but the popularity of smart phones, and will be beneficial to the treatment of the widely distributed and large number of insomnia people in China, as well as to empower primary medical institutions to carry out standardized and effective insomnia treatment, in line with China's "Healthy China" strategic plan. Strategic planning. However, there are few mature dCBT-I in China, and there is a lack of data on the efficacy of dCBT-I for chronic insomnia patients in China.

To initially explore the effectiveness of smartphone-based dCBT-I therapy for chronic insomnia patients in China, we propose to conduct a randomized, open clinical trial study using a Chinese App "resleep" that meets the above requirements, with a general sleep education group as a parallel control group.

"Resleep" is developed by Shenzhen Zeen Health Technology Co., Ltd. With independent intellectual property rights, based on CBT-I theory, combined with algorithmic technology, we can develop individualized treatment plans for patients based on the sleep and behavioral data of a large number of people with insomnia. Unlike traditional CBT-I which is completed in 6-8 weeks through outpatient appointments, users can open the "resleep" App at any convenient time of the day and receive treatment plans by interacting with the chatbot, with each communication taking about 10-15 minutes. The program collects and analyzes the patient's sleep habits, insomnia and sleep cognition during each conversation, and then integrates the five parts of the CBT-I core curriculum step by step to give individualized guidance and complete the treatment in about 4-6 weeks. Moreover, patients' treatment response and changes in sleep data are tracked and analyzed during the treatment period, and the program is continuously adjusted. Preliminary data showed that 85% of patients had significant improvement in subjective sleep quality within two weeks, and no significant adverse effects were found.

## II. Purpose of the study

To explore the effectiveness of digital CBT-I therapy based on smartphone application for chronic insomnia patients in China.

### 101 **III. Research Methodology**

#### 102 **3.1 Research Design Methodology**

103 Randomized, parallel controlled study.

104

#### 105 **3.2 Study site for data collection**

106 Study duration: February 2021 or after ethics committee approval - August 2022

107 Subject recruitment period: February 2021 or after ethics committee approval - August 2021

108 Data collection site:

- 109 ● Demographic data, medical history, questionnaire evaluation: Sleep Monitoring Unit,  
110 Department of Respiratory Medicine, Peking University Hospital
- 111 ● Sleep diary, sleep and symptom profile during treatment: App, smart bracelet

112

#### 113 **3.3 Research Subjects**

114 3.3.1 Inclusion criteria for study subjects: all of the following were met before inclusion.

- 115 ● Age  $\geq 18$  years old.
- 116 ● Meets the diagnostic criteria for chronic insomnia disorder in the ICSD-3: Problems falling  
117 asleep or difficulty maintaining sleep for  $\geq 3$  months ( $\geq 3$  times per week) despite having access  
118 to sleep, it is also accompanied by impaired daytime function.
- 119 ● Insomnia Severity Index (ISI)  $> 14$  points.
- 120 ● If other sleep or psychiatric disorders are present, they need to be stable and have no  
121 requirement for medication.
- 122 ● Proficient in using mobile App, comfortable reading, filling out electronic questionnaires,  
123 communicating and fully understanding the content.
- 124 ● Sign the informed consent form.

125 3.3.2 Exclusion criteria for study subjects:  $\geq 1$  of the following were met, then they could not be  
126 enrolled.

- 127 ● Any of the following conditions currently exist: shift work, alcohol abuse, substance abuse,  
128 overt suicidal ideation, bipolar disorder, aggressive behavior, mania, schizophrenia.
- 129 ● Presence of a diagnosed significant physical illness that interferes with sleep, such as cranial  
130 disease or trauma, cancer pain, unstable angina, uncontrolled cardiac insufficiency, etc.
- 131 ● Being or previously treated with CBT-I.
- 132 ● Epworth Sleepiness Scale (ESS) score  $\geq 12$ .
- 133 ● Informed consent was not signed.

134

#### 135 **3.4 Interventions**

- 136 ● Intervention group: a 6-week dCBT-I implemented by a smartphone App, consisting of sleep  
137 hygiene education, stimulation control, relaxation therapy, sleep restriction therapy and  
138 cognitive therapy. The App uses chatbot to talk to subjects and individualize adjustments by  
139 algorithmically analyzing patient data and feedback.
- 140 ● Control group: received sleep hygiene education and stimulus control knowledge available at  
141 routine clinic visits, with relevant content overlapping with the corresponding modules within  
142 the CBT-I.
- 143 ● The study had no requirements for the medication the patient was receiving.

144

### 145 3.5 Research Indicators

146 3.5.1 Primary endpoint indicator: insomnia severity index (ISI)

147 3.5.2 Other study metrics:

- 148 ● Online sleep diary (7d): total time in bed (TIB), total sleep time (TST), sleep efficiency (SE),  
149 and total time awake (TWT) were calculated from the sleep diary
- 150 ● Smart bracelet recorded: total sleep time, number of times waking up during sleep, wake up  
151 time and sleep quality.
- 152 ● Simplified Sleep Attitudes and Beliefs Questionnaire (DBAS-16)
- 153 ● Fatigue Severity Scale (FSS)
- 154 ● Quality of Life Questionnaire (SF-12)
- 155 ● Generalized Anxiety Disorder Assessment (GAD-7)
- 156 ● Patient Health Questionnaire (PHQ-9 Depression Screening)

157 3.5.3 Other information to be collected: age, sex, education, employment status, living and residence  
158 status, demographic data, current medical history, past medical history and medication, smoking and  
159 alcohol consumption, body mass index (BMI), etc., and adverse effects during treatment.

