### 160 3.6 Research Plan

- 161 ● Patients were recruited by subject recruitment advertisements and sleep clinics, interviewed in  
162 person, screened after signing informed consent, and demographic data, medical history, and  
163 clinical information were collected on the day of screening.
- 164 ● Those who met the inclusion criteria were randomly assigned to the group after recording a  
165 sleep diary for at least 3 days.
- 166 ● A bracelet was issued on the day of enrollment, instructions were given to download the app,  
167 and access to the appropriate group was logged in based on the randomization number. A  
168 6-week period of dCBT-I or sleep education was started on the day of enrollment, and  
169 compliance and efficacy were monitored by investigators without intervention.
- 170 ● Follow-up schedule(online/offline): at the end of the intervention, 1 month, 3 months, and 6  
171 months after the end of the intervention.
- 172 ● Study endpoint: 6 months after the end of the intervention.
- 173 ● Clinical information related to study indicators included: symptoms, physical examination and  
174 medication information, scale assessments (ISI, DBAS-16, FSS, SF-12, GAD-7, PHQ-9), sleep  
175 diary, and bracelet recording of sleep indicators. The time points for collection were: baseline,  
176 at the end of the intervention, 1 month, 3 months and 6 months after the end of the  
177 intervention.
- 178 ● Follow-up continued for 6 months after the end of the study (1 year after the end of the  
179 intervention) and subjects who volunteered to participate completed symptoms online scale  
180 assessments (ISI, DBAS-16, FSS, SF-12, GAD-7, PHQ-9) and recorded a 1-week sleep diary.

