## 215 IV. Participants Protection

- 216 1. This protocol is subject to approval by the Ethics Committee and informed consent signed by  
217 the participants.
- 218 2. Participants' interests.
  - 219 ● The software intervention is delivered primarily through patient education and behavioral  
220 instruction, and the content is set according to the guideline-recommended first-line  
221 treatment protocol specifications. All subjects will receive sleep education to facilitate  
222 and benefit from self-management.
  - 223 ● There will be up to 4 in-person visits during the study period, and subjects will be  
224 compensated for their transportation.
  - 225 ● At the end of the study, all subjects who enroll and complete the study receive a  
226 study-issued smart bracelet.
- 227 3. Possible risks for the subjects: Theoretically, according to the characteristics of CBT-I  
228 treatment, there is a possibility of sleep deprivation or consequent induction of mood disorders  
229 during the sleep restriction treatment sessions. However, according to previous literature, no  
230 significant adverse effects have been reported in clinical studies with similar software abroad.

231 Moreover, the App will adjust the intensity of sleep restriction or discontinue the session if  
 232 necessary based on daily patient feedback, reducing the risk of significant adverse effects.  
 233 4. Subjects may withdraw from the study at any time and for any reason, at their own discretion  
 234 and without any consequences. The decision to withdraw a subject from the study may be  
 235 made by the investigator for urgent medical reasons.  
 236 5. All raw data were de-identified and entered by the Department of Respiratory and Critical  
 237 Care Medicine of Peking University First Hospital. The Shenzhen Zeen Health Technology  
 238 Co., Ltd. was not involved in any statistical analysis or interpretation of the data.

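### Adverse effects are specified for the 6-week treatment period, with no stated recording of new or unresolved events through to the 6-month study endpoint

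*Protocol*

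**What the plan says.** Adverse effects appear as an item to be collected in one place, the end of the list in Protocol Section 3.5.3: "alcohol consumption, body mass index (BMI), etc., and adverse effects during treatment". Section 3.6 fixes the length of treatment: "6-week period of dCBT-I or sleep education was started on the day of enrollment". The same section sets the end of the study later: "Study endpoint: 6 months after the end of the intervention".

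Section 3.6 then lists what is gathered at baseline, at the end of the intervention, and at 1, 3 and 6 months. The list opens "Clinical information related to study indicators included: symptoms, physical examination and" and goes on to "medication information, scale assessments (ISI, DBAS-16, FSS, SF-12, GAD-7, PHQ-9), sleep" diary and bracelet data. Adverse effects are not in it, and neither is the follow-up of unresolved ones. A voluntary extension is also described ("Follow-up continued for 6 months after the end of the study (1 year after the end of the" intervention), with symptoms, scales and a one-week diary.

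On risk, Section IV, item 3, says that with this kind of "treatment, there is a possibility of sleep deprivation or consequent induction of mood disorders", and places this in the sleep restriction sessions. It adds that the App can adjust or discontinue these sessions on daily feedback. The background in Section I describes CBT-I as "providing patients with tools that can be applied in the future".

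**The concern.** Efficacy is followed to 6 months after the intervention, while the stated provision for adverse effects names the treatment period. If the trial is run as written, an event that begins after week 6 need not be recorded as an adverse effect. An event still open at week 6 has no stated route to a recorded outcome.

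The Protocol itself describes a mood disorder as a possible consequence of sleep deprivation. One that began late in treatment could be open when the window ends, whether or not the patient used the techniques again. Section 3.3.1 also admits patients with other psychiatric disorders that are stable and need no medication, so the outcome of such an event would be of interest.

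At stake is the balance of the final report. It could show 6-month benefit beside a 6-week harm record, and a general statement about safety over the study would have formal support for only part of that time. This is a matter for the protocol and cannot be left to an analysis plan, because analysis cannot recover events that nobody asked about.

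**Working it through.** The Protocol gives no figure for the share of follow-up covered by adverse-effect collection, so there is none to reproduce. The check is a count of weeks and a comparison of sections.

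**Inputs**
- Treatment period: 6 weeks (Sections 3.4 and 3.6).
- Study endpoint: 6 months after the end of the intervention (Section 3.6).
- Assumption: one calendar month = 30.4375 / 7 = 4.35 weeks. A 4-week month is used as the alternative.

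**Share of scheduled time covered**

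Share = treatment weeks / (treatment weeks + follow-up weeks).

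- Calendar months: 6 × 4.35 = 26.1 weeks of follow-up; total 6 + 26.1 = 32.1 weeks; share 6 / 32.1 = 18.7%, leaving 81.3%.
- Four-week months: 6 × 4 = 24 weeks; total 30 weeks; share 6 / 30 = 20%, leaving 80%.

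The share is therefore about 19% to 20% under either convention.

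**Gaps between visits after treatment**
- End of intervention to 1 month: 1 × 4.35 = about 4 weeks.
- 1 to 3 months: 2 × 4.35 = about 9 weeks.
- 3 to 6 months: 3 × 4.35 = about 13 weeks.

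Section 3.6 ties its items to fixed dates and states no recall period for symptoms. An event that starts and resolves within one of these gaps could go unrecorded.

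**What is named at each stage**

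| Item | Treatment (weeks 0 to 6) | End of intervention, 1, 3, 6 months |
|---|---|---|
| Adverse effects | Yes (3.5.3) | Not named |
| Outcome of events open at week 6 | Not applicable | Not named |
| Symptoms, examination, medication | See right | Yes (3.6) |
| PHQ-9, GAD-7, FSS | See right | Yes (3.6) |

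The last two rows are also collected at baseline. They show that safety-relevant measurements continue to the study endpoint. What is missing is any instruction to classify a change in them as an adverse effect, with dates and outcome.

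**The case against.** The strongest reply is that the limit is inferred. Section 3.5.3 is a loose list that sets no stop date. Section 3.2 uses the same treatment-period wording for the sleep diary and symptom profile, although Section 3.6 collects diary, bracelet and symptom data through 6 months. Moreover, the Section 3.6 list concerns the study indicators, whereas adverse effects sit under other information, so their absence from it is weak evidence. This partly stands: a longer window may have been intended. But Section 3.6 expressly carries the diary, bracelet and symptom data into follow-up and does not do so for adverse effects. If a longer window was meant, the text still needs to say so.

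A second reply is that late harm would largely be seen. A reader might infer from Section 3.5.3 that nothing relevant to safety is known after week 6. The document does not support that: symptoms, examination, medication, PHQ-9, GAD-7 and FSS are repeated at 1, 3 and 6 months, with neither arm exempted. A new mood disorder treated elsewhere might well show in the medication record or the scales. What remains is the lack of a formal record with onset and outcome, and the gaps between visits.

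A third reply concerns the risk itself. A reader might infer that patients carry on with sleep restriction unsupervised after week 6. Section I says only that the tools can be used later. That is a general remark about CBT-I and does not report what patients in this trial do. Section IV places the named risk within the sleep restriction sessions, and so inside the window. This stands and lowers the weight of the point.

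Finally, the Protocol plans no claim of safety over the whole study, and a report could properly confine itself to the treatment period. That is correct, and it is the fallback offered under the fix.

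**Conclusion.** The point holds as a minor to moderate gap in safety reporting. As written, formal adverse-effect collection covers 6 of about 32 weeks to the study endpoint (about 19%; 20% with 4-week months), and no section provides for following unresolved events.

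That share measures calendar time. It should not be read as the share of harms missed: the Protocol gives no expected rate of late events, the named risk is placed in the treatment period, and later visits give partial cover. Adding the voluntary year to the denominator (6 / (6 + 52) = about 10%) would make the gap look larger than is fair, because Section 3.6 places that extension after the end of the study.

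The conclusion assumes that Sections 3.5.3 and 3.6 would be followed literally. It has no bearing on the ISI analysis or on the sample size.

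**What to change.** 1. In Section 3.5.3, state that adverse effects are collected from randomisation to the study endpoint, 6 months after the end of the intervention.
2. In Section 3.6, add the same adverse-effect question in both arms at the end of the intervention and at 1, 3 and 6 months. Ask about the time since the last contact, and record start date, stop date and outcome.
3. State that events still open at week 6 are included and are followed to resolution or to the last visit.

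The cost is a wording change and one short question at four visits already scheduled, which Section 3.6 allows to be online. The downside is that more unrelated events will be recorded, in both arms.

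If the window is not extended, any safety statement in the report should be limited explicitly to the 6-week treatment period.
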